### Sample size

Our target is to enroll up to 400 patients with half randomized to ESI + local anesthetic and half to local anesthetic alone. We determined overall sample size based on the primary outcome (Roland Morris Disability Questionnaire) with two subgroup analyses (race: Caucasian/non-Caucasian; approach: interlaminar/transforaminal). We will use ANCOVA as the primary method of analysis with the following parameters: 85% follow-up at 6 weeks; two-sided Type 1 error rate of α = 0.05; and adjustment for recruitment site and the outcome measured at baseline. For the purpose of sample size estimation, we conservatively assume six-week Roland Morris Disability Questionnaire scores will have a standard deviation of 7.5 for each group and a correlation between baseline scores and six-week scores of 0.3. For the combined (n = 400) assessment of ESI + local anesthetic vs. local anesthetic alone, the LESS study has 83% power to detect between-group mean differences as small as 2.25 points on the Roland Morris Disability Questionnaire.

Subgroup analyses were powered to detect clinically meaning differences between treatments *within *each subgroup; we did not power the study for the hypothesis of a larger treatment effect within one subgroup compared to another (e.g. an interaction). We adjusted the overall two-sided Type 1 error rate of α = 0.05 using a Bonferroni correction for two tests of the data. Using ANCOVA methods, a sample size of n = 200 (100 per group) provides 83% power to detect between-group mean differences of 3.25 points on Roland Morris Disability Questionnaire.

While formal interim analyses of treatment effect are not planned for this study, we will generate blinded variance estimates for the primary outcomes measured at 6 weeks after a minimum of 100 patients have been enrolled. Conservative estimates of outcome variance and 6-week retention utilized in the initial design of the study yielded an overall upper-bound sample size of n = 400. Adaptive sample size re-estimation will be conducted to provide more precise overall sample size requirements given the observed variance and retention rate, while maintaining the overall Type 1 error rate and power for the stated effect sizes [30].

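### With 400 as a ceiling, the blinded re-estimation can lower the sample size but not raise it, so it targets the stated power rather than maintaining it

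*Protocol article*

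**What the plan says.** All of this is in the Sample size section of the protocol article.

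- The ceiling: "Our target is to enroll up to 400 patients with half randomized to ESI + local anesthetic and half to local anesthetic alone". The section later says that conservative variance and retention estimates "yielded an overall upper-bound sample size of n = 400". The Abstract gives the same maximum.
- The planning values: "two-sided Type 1 error rate of α = 0.05", "85% follow-up at 6 weeks", and "we conservatively assume six-week Roland Morris Disability Questionnaire scores will have a standard deviation of 7.5 for each group", with a baseline to six-week correlation of 0.3. The stated result is 83% power for a 2.25-point difference overall. For subgroups of 200 it is 83% for 3.25 points, with a Bonferroni correction for two tests.
- The look: blinded variance estimates are made for the "primary outcomes measured at 6 weeks after a minimum of 100 patients have been enrolled".
- The claim: the size is then re-estimated from the observed variance and retention "while maintaining the overall Type 1 error rate and power for the stated effect sizes".

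The section mentions no increase above 400. It sets the earliest time of the look by enrolment, not by the number of six-week outcomes.

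**The concern.** A re-estimation maintains power only if it can move the sample size both ways. Here a high variance estimate leaves the size at 400, while a low one, including one that is low by chance, reduces it. Because 400 is only just enough at the planning values, the upward half of the correction is missing.

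Two things are at stake. A reader of the article may believe that power is protected against a larger variance or poorer retention, which it is not. And an early, imprecise variance estimate could stop recruitment short in a trial that would have had adequate power at 400.

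**Working it through.** **1. Reproduce the stated power.** Adjusted SD = 7.5 × √(1 − 0.3²) = 7.155. Evaluable per arm = 200 × 0.85 = 170. Standard error = 7.155 × √(2/170) = 0.776. Power = Φ(2.25/0.776 − 1.960) = Φ(0.939) = 82.6%, which agrees with 83%.

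The total needed for exactly 83% is 4 × 7.155² × (1.960 + 0.954)² / 2.25² / 0.85, or about 404. So 400 has no reserve.

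**2. Power at the ceiling when the planning values are missed** (same formula):

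| SD | Retention | Power at 400 | Total needed for 83% |
|---|---|---|---|
| 7.0 | 85% | 87.4% | about 352 |
| 7.5 | 85% | 82.6% | about 404 |
| 8.0 | 85% | 77.6% | about 460 |
| 8.5 | 85% | 72.5% | about 519 |
| 7.5 | 80% | 80.3% | – |
| 7.5 | 75% | 77.7% | – |

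**3. Information at the look (assumed).** The Abstract plans up to 400 patients over 2 years, or 400/104 = 3.85 a week if accrual is uniform, so about 23 in six weeks. At the 100th enrolment, (100 − 23) × 0.85 is about 65 outcomes. If all 100 have passed six weeks, there are 85. With 65 to 85 outcomes, an estimate of a true SD of 7.5 lies between about 6.2–6.4 and 8.6–8.8 in 95% of samples.

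**4. Chance of a harmful cut at SD 7.5.** A blinded one-sample variance also contains a quarter of the squared effect, so its expectation is 51.19 + 2.25²/4 = 52.45. The new total is 7.894 × the estimated variance, capped at 400. Power of 80% needs a total of about 374, so it is lost when the estimate is below 374/7.894 = 47.3, which is 0.90 of its expectation. With 64 or 84 degrees of freedom, a scaled chi-square falls below that with probability 30% or 27%.

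**5. Whole rule** (400,000 draws per case, sized on 2.25 points, cap 400, retention fixed at 85%):

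| SD | Mean total | Mean power | Chance under 80% |
|---|---|---|---|
| 6.5 | 312–313 | 83.0–83.4% | 25–29% |
| 7.0 | 351–353 | 82.2–82.6% | 26–30% |
| 7.5 | 378–381 | 80.2–80.6% | 27–30% |
| 8.0 | 392–395 | 76.7–77.0% | 100% |

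The first figure in each range is mostly for 65 outcomes and the second for 85; for the last column the order is reversed. If retention is estimated too, SD 7.5 gives 80.0–80.5% mean power and 28–31% under 80%. If the effect term is removed from the variance, it gives 79.5–80.0% and 33–36%. Without the cap and with the effect term kept, mean power at SD 7.5 is about 83%, so the cap causes the average loss.

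**6. Sizing on both stated effects.** With two equal subgroups, alpha 0.025 and 85% retention, the 3.25-point target needs a total of 8 × 51.19 × (2.241 + 0.954)² / 3.25² / 0.85, or about 466 at SD 7.5. Taking the larger requirement, capped at 400, gives mean overall power of 81.9–82.1% and a 7–10% chance under 80%. Without the retention inflation, the subgroup target needs about 396, the overall target governs, and this protection vanishes.

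**The case against.** The strongest reply is that the plan calls both the SD of 7.5 and the retention figure conservative. It starts from a pessimistic size and shrinks if the data allow. Within that range the reply is right about averages: at SD 7.0 or less, mean power stays near the stated 83%. A reader might infer that the rule can never hold the stated power; the planning statement and the figures in step 5 do not support that.

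Other limits also stand:

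- The 65 to 85 outcomes are derived, not stated. One hundred enrolled is a minimum. A later look or slower early accrual gives more data; with 120 outcomes, mean power at SD 7.5 is 81.1%.
- The loss at SD 8.0 or 8.5 is that of any fixed trial of 400. Re-estimation does not create it; it only fails to repair it.
- The article does not say whether the subgroup effect enters the sizing, and step 6 shows how much this matters.
- The text does not expressly forbid exceeding 400, although a ceiling is its natural reading.
- The algorithm and any minimum size may be in the full protocol or the analysis plan. Their absence from the article is not the point.
- The type 1 error half of the claim is not in question, since a blinded variance look has a negligible effect on it.

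What remains is that the article itself states the ceiling, a trigger based on enrolment, and a power guarantee that the ceiling cannot deliver. The conservative SD also does not remove single-trial risk: at SD 7.0, a trial with 87% power at 400 still has a 26–30% chance of being cut to below 80% when sized on the overall effect alone.

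**Conclusion.** The concern holds in a limited form. Maintained power is not a property of this design. The 83% is lost if the SD exceeds 7.5 or retention is below 85%.

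At the planning values themselves, the average loss is modest, from 82.6% to about 80–81%, with a 27–31% chance that the trial ends under 80%. That result assumes a look at the minimum enrolment, sizing on the 2.25-point effect only, a one-sample blinded variance and 400 as a firm cap. Sizing also on the subgroup effect with retention inflation reduces the chance to about 7–10%.

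If the SD is 7.0 or less, average power is held at about 82–83.5%, and the remaining problem is a chance cut in a single trial (about 25–30%). The point deserves correction because the claim is wrong as worded and the remedy is cheap. It does not show that the trial is underpowered.

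**What to change.** 1. Replace *maintaining* with *targeting, subject to the cap of 400*, and state power at the cap for an SD of 8.0 (78%) and 8.5 (73%).
2. Trigger the look on a stated number of observed six-week outcomes instead of enrolments.
3. Guard against chance reductions. One workable choice is a single look at about 170 outcomes (200 × 0.85, so about 200 enrolled plus the six-week lag), using the upper one-sided 80% confidence limit of the blinded residual SD. At SD 7.5 this gives mean power of about 82.3%, a 4% chance under 80% and a mean total of 397. The values 170 and 80% are an example, not a requirement; a minimum total size would serve the same purpose.
4. State whether the re-estimated size must also meet the subgroup target, and whether that target is inflated for loss to follow-up.

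The cost is some wording, a later look and a smaller expected saving: a mean total of about 382 instead of 350 at SD 7.0, and 344 instead of 312 at SD 6.5. The total never exceeds 400.

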## Discussion

As there has been scant research focusing on ESI in older adults with pain due to spinal stenosis, little is known about treatment risks and benefits for this population. Although it has been demonstrated that surgery can be effective for severe spinal stenosis, there are many elderly patients for whom surgery carries substantial risk. There is a need for safer, less-invasive treatment options for older adults with the hope of reducing functional disability and promoting independence. Although ESI is a promising treatment alternative and is widely used in clinical practice, its effectiveness is unknown. Compared to young and middle-age adults, a much higher percentage of older adults have co-morbid conditions such as diabetes that may increase the risks due to systemic absorption of corticosteroids.

As in most clinical trials, we anticipate that recruitment may be a challenge. Patients suffering from pain may be reluctant to delay what they might consider to be definitive therapy. We have developed strategies to increase our chances of successful recruitment including the use of a patient-education video, which was a successful strategy in our prior trials [29]. We have multiple clinical recruitment sites and have added additional clinical sites to attain our recruitment targets. We also have included an optional crossover design to maximize our ability to recruit patients with severe pain into the trial.

The results of this study should provide compelling evidence as to whether or not epidural steroid injections are effective in improving function and pain in the elderly with lumbar spinal stenosis. The LESS trial will provide high-quality data for shorter-term outcomes (six weeks) and longer-term (one-year) outcomes. The patient-reported outcomes, the electronic medical and pharmacy utilization records, and supporting economic data providing reimbursed amounts for resources used will enable a robust evaluation of the comparative benefits and harms associated with epidural steroid injections with anesthetic versus local anesthetic alone.

## Abbreviations

ANCOVA: Analysis of co-variance; BOLD: Back pain Outcomes using Longitudinal Data; BPI: Brief Pain Inventory Interference; CEA: Cost effectiveness analysis; ESI: Epidural steroid injection; GAD-7: Generalized Anxiety Disorder measure; LESS: Lumbar Epidural steroid injections for Spinal Stenosis; PHQ-8: Patient Health Questionnaire (PHQ-8); SSSQ: Swiss Spinal Stenosis Questionnaire (SSSQ); NRS: Numerical rating scale; QALY: Quality adjusted life year.
